### 2.3. Sample size

The sample size for the NARN’ia study was informed by similar studies using doubly labeled water (DLW) and accelerometry to assess energy expenditure and physical activity in adolescents, particularly in low- and middle-income countries [55,68–70]. Studies in comparable populations have used sample sizes ranging from 21 to 60 participants. Given the complexity and high cost of DLW analysis and the logistical challenges of conducting field-based research in rural Nigeria, we selected a target recruitment sample size of n = 70 as both practical and methodologically robust. Power analyses conducted using G*Power software (version 3.1) indicate that a sample size of 70 achieves approximately 70–91% power to detect medium effects in multiple linear regression models at a significance level of α = 0.05 when testing between 2–4 predictors [71]. This sample size is expected to be sufficient to detect meaningful associations between total energy expenditure and key variables such as body composition, physical activity, dietary intake, and age etc., while balancing the practical constraints of cost and logistics of conducting research in rural Nigeria with scientific rigor.

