### 2.2. Study participants

The NARN’ia study is being conducted in Ikwuano Local Government Area of Abia State, located in southeast Nigeria. Ikwuano is a rural region primarily inhabited by crop farmers and traders from the Igbo ethnic group. The recruitment goal for the NARN’ia study is a total of 70 adolescent girls selected from four secondary schools in Ikwuano. The schools were selected in consultation with local education authorities based on geographic spread, accessibility, school size, and willingness to participate. Within each selected school, eligible participants are identified. From this pool, students are randomly selected through balloting without replacement.

Inclusion criteria include female students between the ages of 10 and 19 years who provide verbal assent and have written parental consent. Exclusion criteria include students with physical disabilities, those who are ill during the study period, and students attending boarding schools due to their more restricted living conditions.

Due to logistical constraints particularly the delayed and phased delivery of research materials from Duke University to the study site at MOUAU, the study is being conducted in two phases. This phased approach also allows the local team to manage recruitment and data collection more effectively. Importantly, both phases follow the same recruitment procedures, inclusion and exclusion criteria, and data collection methodology to ensure consistency and comparability of results.

In Phase 1, which took place in early 2024, 40 participants were recruited from four secondary schools. In Phase 2, an additional 20 participants are being recruited beginning in early 2025. In both phases, the same types of data are collected, including anthropometric measurements (height, weight, body composition), assessments of physical activity levels, and 24-hour dietary recalls. There are also no methodological differences between the two phases.

The study team has also considered the potential influence of seasonal factors, such as school holidays and variations in food availability and physical activity patterns, particularly between the dry and rainy seasons in Nigeria. While both phases are scheduled to occur during the school term to ensure access to participants and minimize variability due to holidays, possible seasonal differences in food consumption and activity patterns will be documented and statistically accounted for in the final analysis.

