#### 3.3.2. Fat free mass and fat mass.

The measured BM and calculated TBW will be used to calculate FFM and FM. FFM will be derived from TBW using a hydration coefficient (0.732) [40] i.e., the fraction of FFM comprised of water [40,83,84]. FM will be derived by subtracting FFM from BM and its percentage will also be derived [40]:

$$\text{FFM }(\text{kg})\;=\;\frac{\text{TBW}}{\text{hydration coefficent}}$$
(1)

Thus,

FM (kg) = BM−FFM
(2)

$$∴\text{ FM }(\%)\;=\;\frac{\text{FM}}{\text{BW}}\text{ x 100}$$
(3)

The participants FM percentages will be categorized into 4 categories: under fat, normal fat, over fat, and obese using reference curves [85].

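### The 91% upper end of the stated power range does not reproduce: at n = 70, testing 2 predictors gives about 82%

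*Protocol article*

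**What the plan says.** Section 2.3 (Sample size) gives n = 70 as the recruitment target and supports it in two ways. The first is precedent: comparable studies enrolled 21 to 60 participants, and doubly labeled water is costly and hard to use in the field. The second is a G*Power 3.1 calculation, reported as "a sample size of 70 achieves approximately 70–91% power to detect medium effects in multiple linear regression models". The test level is 5%, and the range is tied to the number of predictors under test, two to four.

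The section gives no numeric value for a medium effect. It also does not say which G*Power regression test was used: all predictors jointly, a subset, or one coefficient. It names body composition, physical activity, dietary intake and age as examples of variables to be related to total energy expenditure. Section 2.2 (Study participants) adds that "possible seasonal differences in food consumption and activity patterns will be documented and statistically accounted for in the final analysis". Neither section writes out a regression model.

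**The concern.** For a fixed sample size, effect size and α, power in a multiple regression F test falls as the number of tested predictors rises. A range quoted for 2 to 4 predictors should therefore have the 4-predictor power at its lower end and the 2-predictor power at its upper end. A spread of 21 points (91 − 70) looked too wide for that step.

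This is the only power figure in the article, and the text relies on it, together with precedent and cost, in calling the target "we selected a target recruitment sample size of n = 70 as both practical and methodologically robust". At 91% power, a true medium effect would be missed 9% of the time. If the real figure is about 82%, the miss rate is about 18%, or twice as high. A null association from a two-predictor test would then be read with more confidence than the design supports.

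**Working it through.** **Inputs.** From section 2.3: n = 70, α = 0.05, u = 2 to 4 tested predictors, stated power 70–91%. Assumed: *medium* means the usual convention f² = 0.15 (R² = 0.15/1.15 ≈ 0.13), and the test is the overall F test for R² different from zero.

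**Formula.** Noncentrality λ = f²·n = 0.15 × 70 = 10.5. Degrees of freedom are u and v = n − u − 1. Power = P[F′(u, v; λ) > F₀.₉₅(u, v)], where F′ is the noncentral F distribution.

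**The lower end first.** With u = 4, v = 65 and λ = 10.5, power is 70.4%. The stated 70% reproduces. Solving in the other direction, exactly 70% with 4 predictors needs f² = 0.149, which supports reading *medium* as 0.15.

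**The rest of the range, same calculation.**

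| Tested predictors u | v | Power |
|---|---|---|
| 2 | 67 | 81.7% |
| 3 | 66 | 75.6% |
| 4 | 65 | 70.4% |

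Upper end: 91 − 81.7 = 9.3 points too high. Implied miss rate: 100 − 91 = 9%. Computed miss rate: 100 − 81.7 = 18.3%.

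**What 91% with 2 predictors would need.** Either n = 91, or f² = 0.196 at n = 70. At f² = 0.196, 4 predictors have 83% power, so the 70% end is lost.

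**Other readings at n = 70 unless stated.**

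| Reading | 2 predictors | 4 predictors |
|---|---|---|
| R² = 0.13 exactly (f² = 0.149) | 81.5% | 70.2% |
| Random-predictor model, R² = 0.13 | about 80% | about 69% |
| α = 0.10, overall F test | 89.1% | about 81% |
| One coefficient, two-sided, in a model of this size | 89.1% | 89.1% |
| One coefficient, one-sided, in a model of this size | 94.1% | 94.1% |
| n = 60, overall F test | 74.7% | 62.1% |

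A one-sided test of one coefficient at n = 60 does give about 90.6%. It departs from the stated n and from the stated number of tested predictors, and it too is flat across model size. None of these readings gives both 70% and 91% over 2 to 4 tested predictors.

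**Effect of extra terms at f² = 0.15, n = 70.** Testing five terms jointly gives 65.9%. Adjustment covariates that are not themselves tested cost one residual degree of freedom each: 4 tested in a model of 6 keep 70.3%, and 2 tested in a model of 6 keep 81.6%.

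**The case against.** The best defence is that the 91% came from a different test. A two-sided test of a single coefficient gives 89.1%, within 2 points of the stated figure, and the article specifies neither f² nor the test. This may well explain the number as a reporting slip. It does not rescue the sentence, which speaks of testing 2 to 4 predictors. The one-coefficient figure barely moves with model size and so cannot be one end of a range indexed by the number of predictors. A range that mixes two tests still misstates the power for 2.

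It is also fair to say that the error touches only the favourable end. The 70% is printed and correct, precedent and cost carry part of the justification, and the main aim is to measure energy requirements rather than to run a confirmatory regression. All of that stands, and it limits how much weight the point deserves.

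A reader might go further and infer that the plan's own variables make six or more terms, with power near 62%. The documents do not support this. Section 3.3.2 says "The measured BM and calculated TBW will be used to calculate FFM and FM", which describes how the two quantities are derived, not that both enter a regression. Section 2.2 promises to account for season but does not place a season term in a model of total energy expenditure. The figure of 61.8% applies only to a joint test of all six terms.

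**Conclusion.** The upper end of the power statement is wrong as written. On the article's own n, α and predictor range, with f² = 0.15, the supported range is about 70–82% for 4 down to 2 tested predictors. The overstatement is about 9 points at the upper end and nil at the lower end.

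The conclusion assumes f² = 0.15 and the overall F test. The first is supported by the lower end reproducing. Neither is decisive, because no other single effect size or test examined gives both stated ends.

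The point does not show that the 70% lower end is too high for the planned analysis, or that 70 participants are too few. Power would fall below it, to about 66%, only if a fifth term were tested jointly with the four named variables; adjusting for season alone costs almost nothing. This is a correction to a published figure, of moderate weight, and it alters no enrolment decision.

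**What to change.** Correct the power sentence in section 2.3 along these lines:

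> At n = 70 and α = 0.05, the overall F test in multiple linear regression has about 82%, 76% and 70% power to detect f² = 0.15 when 2, 3 and 4 predictors, respectively, are tested.

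If the upper figure came from a test of one coefficient, report it in a separate sentence as about 89% (two-sided, f² = 0.15) and label it as such. If another effect size or test was used, name it and give the figures it produces for 2, 3 and 4 tested predictors. Optionally, add that a joint test of five terms would have about 66% power, and that untested adjustment covariates such as season leave the figures almost unchanged.

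The cost is one or two sentences and a slightly less favourable best case. No participants are added; section 5 reports that Phase 2 recruitment is already complete.

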### 2.4. Data and sample collection

#### 2.4.1. Total energy expenditure.

Data and sample collection will take place three times over a ten-day period between March 7 and May 13, 2024 (Fig 1). On the morning of days 1, 5, and 10, participants will be transported to the Nutrition Assessment Laboratory at the Department of Human Nutrition and Dietetics, Michael Okpara University of Agriculture, Umudike (MOUAU) where data collection will take place. On Day 1, participants will be required to fast beforehand although they will be allowed to drink water.

**Fig 1 pone.0333889.g001:**
[figure not shown]
Timeline of Data Collection. DLW is administered and urine samples are collected 0ver a 10-day period. Additionally, socio-demographic, dietary, anthropometric, and activity data are collected.

First, participants will provide ~5 ml of pre-dose urine which will be used to determine each of their isotopic baselines. The time of this and all subsequent urine sample collections will be recorded accurately to the nearest minute. Next, participants will be weighed using an Omron Body Composition Monitor and Scale (BF-511) to the nearest 0.1%. This is a bioelectrical impedance scale that estimates the percentage of body fat, muscle mass, and other tissues in the body by sending a low-level electrical current through the body and measuring the resistance (impedance) to the current flow. Different tissues in the body, conduct electricity differently for example, muscle tissue, which contains more water, conducts electricity better than fat tissue. By analyzing the impedance, the scale can estimate the proportion of different tissues within the body [72]. A dose of DLW (6% H_2_-^18^O, 10% ^2^ H_2_-O) tailored to their body mass at 1 ml per/ kg will be administered to each participant also at a recorded time. While waiting for the DLW to equilibrate in the body, participants will be provided with food and water, and the rest of the data collection will continue. Approximately 6 hours after DLW dose administration, participants will provide another urine sample. On days 5 and 10, participants will not be required to fast before urine sample collection. Samples will be stored and shipped cold (2–8 °C) to the [name] Lab at Duke University, USA for isotope enrichment analysis via laser-absorption mass spectrometry. Depletion rates of ^2^H and ^18^O will be used to calculate each participant’s rate of CO_2_ production over the 10-day study period.

#### 2.4.2. Socio-demographic characteristics.

During the waiting period between DLW dosing and the first post-dose urine collection, participants will be asked to fill out a socio-demographic characteristics survey adapted [73]. Trained research assistants will assist participants in filling out the survey with information about their age, household size, parents’ education, occupation, and income.

#### 2.4.3. Dietary assessment.

A 24-hour dietary recall will be conducted electronically using the International Dietary Data Expansion (INDDEX24) Dietary Assessment mobile application on the days of data collection, utilizing the multiple pass method [18]. During the first pass, participants will be asked to recall all the foods and beverages they consumed in general terms, using local meal/recipe names and brand names. In subsequent passes, more detailed information about each food item will be recorded, including the time and location of consumption, ingredients, methods of preparation, portion sizes, and other food-specific details.

#### 2.4.4. Anthropometric measurements of body composition.

In addition to body mass (BM), additional anthropometric measurements such as height, waist, and hip circumference data, and SFT will be recorded using a height ruler, tape measures, and calipers, respectively. On day 10, after the final urine sample is collected, participants will be weighed again using the bioelectrical impedance scale.

#### 2.4.5. Physical activity level.

Daily physical activity will be tracked using the wrist-worn Axivity AX3 triaxial digital accelerometers during the DLW period. Participants will receive the accelerometers on day 1, along with instructions on proper wear and maintenance. They will be instructed to wear the accelerometer at all times on their non-dominant wrist to minimize noise, and to only take it off for water-based activities. Parents and school staff will be asked to help ensure compliance. The accelerometers will be collected on day 10, and the data will be downloaded for analysis. Additionally, participants will be given a physical activity diary to record wear and non-wear times.

## 3. Data analyses

### 3.1. Dietary assessment

The data collected using the INDDEX 24 App will be analyzed on the INDDEX Dietary Assessment Platform using the Analytical Reports features which provide simple summary statistics of the dietary survey data. The results will be compared against standards of recommended daily energy and nutrient requirements for adolescents [74] to determine the adequacy of energy and nutrient intake.

### 3.2. Accelerometry

Activity log data from the accelerometers will be downloaded as.csv files using the AX3 software and imported into R software [75] for raw accelerometer data processing using the GGIR v.3.1−1 [76,77] package. Analysis will include the quantification of time of non-wear which will be validated against each participant’s physical activity diaries and to estimate times of physical activity, inactivity, and sleep.

### 3.3. Anthropometric Data Analyses

Participants’ body mass index (BMI) will be calculated using WHO (World Health Organization) Anthroplus software and assessed against the WHO BMI-for-age (5–19 years) girls z-score charts into categories of thin (<−1SD), healthy (0), overweight (>+1SD), and obese (>+2SD) [78,79]. Additionally, other anthropometric ratios, such as waist-to-hip ratios, will be calculated and categorized according to the WHO criteria [80]. Waist-to-hip ratios less than 0.85 will be considered healthy, while ratios above 0.85 will be classified as indicating a higher health risk.

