### 1.5. Nutritional challenges in Nigeria

There are approximately 600 million adolescent girls (aged 10–19) worldwide, with nearly 90% residing in developing nations [59]. In Nigeria alone, the number exceeds 25 million, representing about 13% of the total population [60,61]. Adolescents worldwide face numerous nutritional challenges that impact their growth, development, and future health. Undernutrition, micronutrient deficiencies, poor dietary practices, and food insecurity are prevalent in low and middle-income countries (LMICs). Increasingly, these issues coexist with rising obesity rates in LMICs, a phenomenon known as the dual burden of malnutrition [62].

A considerable number of adolescent girls across Africa suffer from chronic malnutrition, severely affecting their health and development. In Nigeria specifically, about 1 in 4 adolescent girls (ages 15–19) are malnourished, and 61% are anemic [63]. Despite these alarming statistics, in Nigeria, similarly to most developing countries, nutrition initiatives have primarily focused on young children and/or adult women, leaving this demographic quite neglected [64]. This neglect is concerning because adolescent girls are particularly vulnerable to malnutrition due to their increased need for nutrients, cultural influences that affect their eating habits, and susceptibility to environmental influences prevalent in impoverished regions [65,66]. Addressing their nutritional needs is a crucial step toward breaking the cycle of intergenerational malnutrition, chronic diseases, and poverty [67]. However, solving these challenges and improving adolescent girl nutrition requires accurate and reliable measures of daily energy needs.

NARN’ia aims to conduct the most comprehensive assessment of energy requirements in adolescent girls in Nigeria to date. This study will integrate dietary assessments using the 24-hour recall method; physical activity levels using accelerometry; anthropometric evaluations of body composition, and the DLW method for assessing both body composition as well as indirect calorimetry. Together, these methods will provide evidence-based data essential for formulating appropriate nutritional guidelines to support healthy growth and development of adolescent girls in Nigeria. Furthermore, this research initiative will establish a foundational framework for future studies on energy requirements in Nigeria and other LMICs.

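### The BMI-for-age classes in section 3.3 leave a gap around the median, overlap at the top, and pool every girl below −1 SD into one ungraded class

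*Protocol article*

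**What the plan says.** Section 3.3 (Anthropometric Data Analyses) has each girl's BMI "assessed against the WHO BMI-for-age (5–19 years) girls z-score charts" and then placed "into categories of thin (<−1SD), healthy (0), overweight (>+1SD), and obese (>+2SD"). References [78,79] are cited for this, but their cut-offs are not reproduced. No other section defines or amends the BMI classes.

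Section 2.2 gives the size of the study: "The recruitment goal for the NARN’ia study is a total of 70 adolescent girls". The same section counts 40 girls in Phase 1 and a further 20 in Phase 2, which makes 60. Both totals are used below.

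**The concern.** A classification rule should give every girl exactly one class. This one does not, for three separate reasons.

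- **Gap.** *Healthy* is given as the value 0, with no interval. The neighbouring classes begin below −1 SD and above +1 SD, so nothing is stated for the range between them except its midpoint.
- **Overlap.** "overweight (>+1SD") has no upper limit, so it contains the whole of *obese*.
- **Unequal grading.** High BMI is split at +1 and +2 SD. Low BMI is not split at all, so mild and marked low BMI cannot be told apart in the results.

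The third matters most here, because the article's motivation is undernutrition. Section 1.5 states that "about 1 in 4 adolescent girls (ages 15–19) are malnourished". A single *thin* percentage would be hard to interpret beside such a figure, because it does not show how many of the girls are only just below −1 SD. The first two mean that two analysts following the text could produce different tables from the same data.

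**Working it through.** The article states no expected share for any class, so there is no figure to reproduce. The check is how much of the z-score scale each printed class covers.

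**Inputs**
- Cuts (section 3.3): below −1, exactly 0, above +1, above +2.
- Reference scale: z taken as standard normal in the reference population. This is an assumption.
- Number of girls: 70 (goal), or 40 + 20 = 60 (phase counts), both from section 2.2.
- Mean *m* and SD *s* of z among the study girls: not given, so a range is shown.

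**Formula.** P(z < c) = Φ((c − m)/s).

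**Step 1: reference population (m = 0, s = 1)**
- *Thin*: Φ(−1) = 0.1587. Of 70 girls, 11.1; of 60, 9.5.
- From −1 to +1: Φ(1) − Φ(−1) = 0.6827. Of 70, 47.8; of 60, 41.0. Read literally, all of these except z exactly 0 have no class.
- Above +2, in two classes at once: 1 − Φ(2) = 0.0228. Of 70, 1.6.

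**Step 2: other readings of 0**
- If 0 means z rounded to the nearest whole number (|z| < 0.5), the class holds Φ(0.5) − Φ(−0.5) = 0.3829. Then 0.6827 − 0.3829 = 0.2998, or 30.0% of the reference, still has no class.
- If 0 stands for the whole band from −1 to +1 SD, and *overweight* stops at +2 SD, the shares are 15.9%, 68.3%, 13.6% and 2.3%. They sum to 100% apart from rounding, with no gap and no overlap.

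**Step 3: what the single low class pools.** The lower side is split at −2 SD, to mirror the +2 SD cut that the plan uses above the median. On the reference, 0.1587 − 0.0228 = 0.1359 lies between −2 and −1 SD (9.5 of 70 girls) and 0.0228 lies below −2 SD (1.6 of 70). So 0.1359/0.1587 = 86% of the girls labelled *thin* would be in the milder band.

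**Step 4: if the study girls differ from the reference (s = 1)**

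| Mean z (assumed) | Below −1 SD | −1 to +1 SD | Above +1 SD | Below −2 SD |
|---|---|---|---|---|
| −1.00 | 50.0% | 47.7% | 2.3% | 15.9% |
| −0.75 | 40.1% | 55.9% | 4.0% | 10.6% |
| −0.50 | 30.9% | 62.5% | 6.7% | 6.7% |
| −0.25 | 22.7% | 66.8% | 10.6% | 4.0% |
| 0 | 15.9% | 68.3% | 15.9% | 2.3% |
| +0.50 | 6.7% | 62.5% | 30.9% | 0.6% |

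For s from 0.9 to 1.2, the share between −1 and +1 SD stays above one half for means from −0.75 to +0.50 (51.0% to 73.3%). It drops below one half at a mean of −1 (45.2% to 48.7%). At a mean of −0.50 with s = 1, the single low class would hold 0.309 × 70 = 21.6 girls, of whom 0.067 × 70 = 4.7 are below −2 SD.

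**The case against.** The strongest reply is that this is loose notation and nothing more. With *thin* below −1 SD and *overweight* above +1 SD on a z-score chart, the 0 most plausibly names the median line of the band between them. No analyst would require a z-score of exactly 0, and most would stop *overweight* at +2 SD. On that reading the gap and overlap vanish, as step 2 shows. This largely stands. A reader might infer that most girls will go unclassified, but that follows only from the literal text. The article still does not state the intended reading, and the low side remains ungraded under it.

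A second reply is that 15.9% is simply what any cut at −1 SD takes from a reference distribution, just as the +1 SD cut takes 15.9% at the top. That stands too: the percentage shows where the cut lies, not that it is wrong. A reader might infer that −1 SD departs from the WHO definition of thinness and so inflates prevalence. The documents do not support this, because the cut in references [78,79] is not quoted. It is a matter for the authors to check.

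A third reply concerns importance. A reader might suppose that prevalence of undernutrition is a headline result, or that TEE will be compared between BMI classes. Neither is stated. The aim is energy requirements, section 2.3 bases the sample size on regression of TEE on several variables, and body fat is classified separately from isotope dilution in the section on fat free mass and fat mass. The malnutrition figure in section 1.5 comes without a criterion, so it neither conflicts with section 3.3 nor shows which cut is intended. This reply stands and limits the severity.

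**Conclusion.** The point holds as a defect in a stated rule. The printed classes have a gap (68.3% of the reference on the literal reading, none if the band from −1 to +1 SD was meant), an overlap above +2 SD (2.3% of the reference), and one undivided low class (15.9% of the reference, about 11 of 70 girls or 9.5 of 60). Only the last survives every reasonable reading of the text.

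The percentages assume normally distributed z-scores and, unless a mean is shown, the reference distribution. The study girls' own distribution is not in the article.

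Severity is moderate to minor. The descriptive results on nutritional status are affected. Design, data collection and TEE estimation are not.

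**What to change.** Replace the list of cuts in section 3.3 with closed, non-overlapping intervals that cover the whole scale:

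- Obese: above +2 SD.
- Overweight: above +1 SD up to and including +2 SD.
- Healthy: an explicit interval, with both limits and the treatment of boundary values stated.
- Low BMI: check the *thin* cut against references [78,79] and correct it if it differs. Whatever label is used, report girls from −2 to −1 SD separately from those below −2 SD, so that mild and marked low BMI are not pooled.

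The cost is one sentence and a few more table rows. Some rows will have small counts (on the reference distribution about 1.6 of 70 girls lie below −2 SD), so they should be given as numbers as well as percentages. The plan already needs each girl's z-score, so no new data are required and the classes can be settled before the final analysis.
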